#### Protection of the rights and health of participants

This is a prospective observational cohort study, so researchers conducting the study will not provide medication or other treatment to participants diagnosed with depression or other mental disorders as part of the study. However, the project will include the following steps to protect the rights and health of participants.A)Fully informed consent. Prior to providing written informed consent to participate in the study, potential participants and their family members will be fully informed about the expectations and potential risks of the study and about their right to drop out of the study at any time for any reason.B)At the time of the diagnostic examination, the examining psychiatrist will inform the participant of the diagnostic result of the exam. Basic information about the symptoms, course and appropriate treatment of the condition will be provided to the participant in a non-technical manner that they can easily understand.C)Participants with current mental disorders who are not receiving treatment will be advised to seek treatment and information about the nearest facilities where they can get mental health treatment will be provided.D)Self-management manuals about depression: manuals containing knowledge about depressive disorders and self-management of depressive moods will be provided.E)Participants will be provided with contact information of study researchers that they can use to contact researchers if they feel depressed or need help.F)For participants considered at high risk of suicide or self-harm, after signing a specific consent form with the participant and his/her family members, the situation will be discussed and the family members will be informed about steps to take to reduce the risk of suicide or self-harm and what they should do and where to seek help if the participant has suicidal or self-harm behavior.G)Standardized management procedure to deal with suicide and self-harm: Our study has standard regulations (approved by the ethical committee to at the Second Xiangya Hospital of Central South University) to deal with suicide and self-harm behaviors of participants.

#### Outcome measurements

The primary outcome of this study is depression. At recruitment, local community doctors will evaluate the mental health of participants, and refer those considered at high-risk for depression (and some of those considered at moderate- or low-risk for depression) to a psychiatrist who will administer the Structured Clinical Interview for DSM-5-CV to determine whether the individual meets the diagnostic criteria of a depressive disorder. At each annual assessment, trained researchers will screen participants through phone calls and self-reported questionnaires, and refer those considered at high-risk of depression to a psychiatrist for a formal diagnostic assessment.

Secondary outcomes include fatal and non-fatal suicidal behavior, other self-harm behaviors, relapses of depression after recovery from a previous episode, and the prevalence and incidence of other types of mental disorders assessed when administering the SCID-5-CV.

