#### Enrollment and baseline evaluation

Residents of the 34 primary sampling sites who meet the inclusion and exclusion criteria will be randomly selected from lists of community members registered in the public health system (described above) and invited to participate in the project. To improve the response rate, prior to the enrolment advertising billboards will be set up at the local health service center and messages introducing the study will be sent to all community members via WeChat (social media) site. Enrollment and baseline data collection included the following steps (see Fig. 2):A)Basic information (e.g., name, age, address, phone number) of residents in the community is extracted from the community health service center (which typically have a registry of virtually all permanent residents in each community).B)Among the permanent residents 18 years of age or older, 3250 individuals will be randomly selected from the registry of residents maintained by the local health authorities.C)Researchers make phone calls to selected residents to introduce the China Depression Cohort Study-I and – if the individual expresses interest in participating – to invite them to the local community health service center for an intake interview. Researchers and community health care workers will make home visits to invite individuals who cannot be contacted by phone.D)When potential participants visit the community clinic they will be provided with details about the project and asked to sign a written informed consent.E)Baseline assessments of consenting participants are typically conducted at the local health clinic on the same day as enrollment. They include the following:Community clinic physicians conduct a physical exam, measuring weight, height, heart rate and blood pressure.Research nurses collect biological samples of blood, urine and faeces.Trained researchers instruct participants in the use of the online Participant Module and supervise their completion of self-report questionnaires about their demographic characteristics, environmental exposures, and mental health symptoms.Community clinic doctors conduct a psychological evaluation using the expanded version of the 12-item General Health Questionnaire (GHQ-12) [34, 35], which consists of the original Chinese version of the GHQ-12, and 12 additional items to improve its sensitivity. The 12 supplemental items include 6 items described in previous studies [34, 36] (respondents' subjective report of their physical health in the past month; respondents' subjective report of their psychological health in the past month; obsessive thoughts or compulsive behaviors in the last month; restriction of activities because of phobias in the past month; feelings of extreme nervousness or anxiety in the last six months; and social problems due to drinking in the last year), and 6 items developed for the current project based on expert consultation (feeling depressed or down for at least two weeks; seeking help from others due to psychological problems; hospitalization due to psychological problems; suicidal behaviors such as self-poisoning or self-injury; intention of self-harm or suicide; family history of mental disorders such as depression). The 12 GHQ-12 items are each scored as 0 (not present or mild) or 1 (present to a moderate or significant degree); so the total GHQ-12 score ranges from 0 to 12. Each participant will be classified as low-risk of depression (a GHQ-12 score of 0 to 1 and none of the 12 additional items present), moderate-risk of depression (a GHQ-12 score of 2 to 4 and none of the 12 additional items present), or high-risk of depression (a GHQ-12 score of at least 5 or a positive score on any of the 12 additional items) [36].Formal diagnostic examination by a psychiatrist using the SCID-5-CV interview schedule will be conducted in all participants classified as high-risk of depression, in 40% participants classified as moderate-risk of depression and in 10% participants classified as low-risk of depression. Similar to other two-stage epidemiological studies [34, 36], higher proportions of individuals at higher risk of depression are administered the definitive diagnostic interview; this method allows for an efficient use of the limited number of psychiatric personnel available while allowing for accurate prevalence estimates for the total population (by estimating the rates of false positive GHQ-12 rates in the high-risk group and rates of false negative GHQ-12 rates in the moderate- and low-risk groups).All high-risk participants are referred for a brain MRI scan at a regional hospital, and low-risk and moderate-risk participants are given the option of a referral for a brain MRI scan.

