#### Follow-up

The initial duration of follow-up is five years. (The study organizers will subsequently apply for additional funding to transform the study into a continuing cohort project.) The follow-up procedures will be as follows:A)Community-level variables shown in Table 2 (including climatic, environmental and socio-economic characteristics) will be collected annually from national databases for each of the 34 primary sampling sites.B)Participants who do not have any current or past mental disorder (based on the SCID-5-CV interview) at baseline or at subsequent assessments, the following follow-up assessments will be made *annually*.Information about participants’ diagnoses and treatment of diseases in the prior year will be collected in three ways: review of records of the national medical insurance system (which covers all permanent residents); self-reported information about medical treatment for mental disorders; and results of the annual GHQ-12 screening and SCID-CV interviews.Community clinic physicians conduct a physical exam, measuring weight, heart rate and blood pressure.Research nurses collect biological samples of blood, urine and faeces from a sample of 5% of the participants.Repeat MRI scans we be conducted in each participant who had MRI scan at baseline.Online questionnaires will be sent to participants through e-mail or WeChat. Participants unable to use this online system will be invited to visit the local health clinic where they will be given equipment and any assistance needed to complete the questionnaires.Trained researchers will make phone calls to those who don’t respond to the online questionnaires and to those who self-report as being at high risk of a depressive disorder at any time over the prior year. Participants classified by the researcher as ‘high-risk of depression’ at any time in the prior year will be encouraged to attend an appointment with a psychiatrist at the community clinic or local general hospital.Psychiatrists will perform SCID-5-CV diagnostic assessments of the invited participants who agree to the interview.C)For participants diagnosed with current or past depressive disorder or other psychiatric disorder based on SCID-5-CV interviews by a psychiatrist at baseline or during follow-up assessments the following follow-up assessments will be conducted.Every 3 months, telephone calls will be performed by trained researchers to check their depressive symptoms, thoughts of suicide or self-harm, suicide attempts or other self-harm behaviors, social functioning, and mental health treatments over the prior 3 months. Individuals classified by the researcher as ‘high-risk of depression’ who have never been diagnosed with a depressive disorder (only had other diagnoses) or have fully recover from a prior episode of depression (i.e., at least 2 months of no clinically significant symptoms) will be encouraged to attend an appointment with a psychiatrist at the community clinic or local general hospital.A psychiatrist will conduct a repeat diagnostic exam (using the SCID-5-CV interview) with invited participants who agree to the interview to determine whether a new-onset major depressive disorder has occurred in the prior 3 months.Each year information about participants’ diagnoses and treatment of diseases (including treatment for mental disorders) from hospital records will be collected from regional hospitals and from the national public health system.Each year community clinic physicians conduct a physical exam, measuring weight, height, heart rate and blood pressure.Each year the standard online questionnaire will be sent to these participants through e-mail or WeChat. Participants unable to use this online system will be invited to visit the local health clinic where they will be given equipment and any assistance needed to complete the questionnaires.Each year research nurses collect biological samples of blood, urine and faeces from participants with a current or lifetime depressive disorder (but NOT from individuals who only have other, non-depressive, mental disorders).Each year, participants with a current or lifetime depressive disorder (but NOT from individuals who only have other, non-depressive, mental disorders), are referred for a brain MRI scan at a regional hospital.

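### Follow-up gives the diagnostic interview only to high-risk participants, so the planned incidence is screen-detected, lacks the baseline false-negative correction, and is understated by an unknown amount

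*Protocol article*

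**What the plan says.** **Baseline.** Under Enrollment and baseline evaluation, the SCID-5-CV is given to all high-risk participants, "in 40% participants classified as moderate-risk of depression and in 10% participants classified as low-risk of depression". The stated reason is to obtain accurate prevalence for the whole population, in part by estimating "rates of false negative GHQ-12 rates in the moderate- and low-risk groups". High risk is defined there as "a GHQ-12 score of at least 5 or a positive score on any of the 12 additional items". The added items include "family history of mental disorders such as depression" and social problems due to drinking.

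**Follow-up.** Outcome measurements says that once a year "trained researchers will screen participants through phone calls and self-reported questionnaires, and refer those considered at high-risk of depression to a psychiatrist". The Follow-up section agrees: participants whom the researcher classes as high-risk "at any time in the prior year will be encouraged to attend an appointment with a psychiatrist", and the psychiatrist interviews those who agree. No interviews of moderate- or low-risk participants are described. For participants without a disorder, diagnoses are also collected from national medical insurance records and from self-reported treatment.

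**Contact schedule.** These participants are assessed annually. For those with any current or past disorder on SCID-5-CV, the plan says "Every 3 months, telephone calls will be performed by trained researchers to check their depressive symptoms".

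**Analysis.** Data analyses estimates national prevalence and incidence with poststratification weights. It uses Cox regression for the association of bio-psycho-social factors with the diagnosis of depression.

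**The concern.** The baseline design accepts that the screen misses cases and pays for interviews of screen-negative participants to measure how many. The follow-up rule drops those interviews. From then on, an untreated case below the high-risk threshold is indistinguishable from a non-case, and follow-up interviews alone cannot show how many there are.

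Two results are exposed. National incidence, a stated product of the first set of analyses, will be too low. Hazard ratios for onset, which serve the first specific aim, may be biased if the chance of being interviewed depends on the factor being studied. A larger cohort reduces neither problem.

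**Working it through.** **1. The plan's own figure.** The only sample size calculation is 79,986 for a prevalence of 2.1% with a 95% interval of 2.0% to 2.2%. An exact (Clopper-Pearson) interval of total width 0.002 gives 79,985.3, which rounds up to 79,986, so the figure is reproduced. It concerns baseline prevalence and neither supports nor weakens this point. The documents give no figure for incidence or for screen sensitivity.

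**2. Interview fractions side by side.**

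| Risk group | Baseline | Follow-up |
|---|---|---|
| High | 100% | 100% referred; those who agree are interviewed |
| Moderate | 40% | none described |
| Low | 10% | none described |

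At baseline, a case found in the moderate group can be weighted by 1/0.40 = 2.5 and one in the low group by 1/0.10 = 10. At follow-up the fraction in both groups is zero, so no such weight exists. Poststratification weights adjust the composition of the sample. They cannot restore cases that were never diagnosed.

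**3. Illustrative size of the undercount.** The shares and annual incidences below are assumptions (low / moderate / high). The calculation takes 85,000 participants, full attendance and no detection through records. Cases in each group = 85,000 × share × incidence; share missed = (low + moderate) / total.

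| Scenario | Shares | Annual incidence | Cases (low / moderate / high) | Missed / total |
|---|---|---|---|---|
| A | 70 / 20 / 10% | 0.1 / 1 / 8% | 59.5 / 170 / 680 | 229.5 / 909.5 = 25% |
| B | 70 / 15 / 15% | 0.2 / 1.5 / 6% | 119 / 191.25 / 765 | 310.25 / 1075.25 = 29% |
| C | 60 / 25 / 15% | 0.05 / 0.5 / 8% | 25.5 / 106.25 / 1020 | 131.75 / 1151.75 = 11% |
| D | 60 / 20 / 20% | 0.3 / 2 / 5% | 153 / 340 / 850 | 493 / 1343 = 37% |

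If records or self-reported treatment found 30% to 50% of these missed cases (also assumed), the 11% would fall to about 8% to 6% and the 37% to about 26% to 18%.

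**4. Illustrative effect on a hazard ratio.** This step applies only if an exposure, such as family history, puts a participant in the high-risk group at follow-up on its own. Take a true hazard ratio of 1, a rare outcome, complete detection in the exposed and screen sensitivity s in the unexposed. The apparent hazard ratio is then about 1/s. If records find a share r of the screen-missed cases, it is about 1/(s + r(1 − s)).

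| s | r = 0 | r = 0.3 | r = 0.5 |
|---|---|---|---|
| 0.9 | 1/0.90 = 1.11 | 1/0.93 = 1.08 | 1/0.95 = 1.05 |
| 0.7 | 1/0.70 = 1.43 | 1/0.79 = 1.27 | 1/0.85 = 1.18 |

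Equal non-attendance in both groups cancels from the ratio.

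**The case against.** The strongest reply is that follow-up does not rest on the interview alone. Insurance records cover all permanent residents, and treatment is also self-reported. This stands in part: it is wrong to infer that every case outside the high-risk group is lost. But these sources find treated cases only and depend on care-seeking, so they reduce the gap without measuring it.

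Second, a reader might infer that anyone with a family history is high-risk every year whatever the symptoms, and that hazard ratios are therefore inflated. The documents do not support that as fact. The rule with the 12 added items is stated for baseline. The follow-up text refers to annual GHQ-12 screening, self-reported high risk and the researcher's classification. The bias in hazard ratios is conditional on the rule actually used.

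Third, a reader might infer a false downward trend from corrected baseline to uncorrected later figures. The plan describes trends in the demographic characteristics of depression; it does not set baseline prevalence against later incidence.

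Fourth, quarterly calls do not amount to four chances of detection against one. Each call covers the prior three months and the annual screen covers the prior year, so both schedules span the whole year. Shorter recall and more frequent contact may still raise detection in those with a prior diagnosis, by an amount that the documents do not let one estimate.

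Finally, the sizes shown are assumed. That objection stands in full.

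**Conclusion.** The point holds for incidence. Followed as written, the plan estimates the incidence of depression that is screened as high-risk and confirmed, or treated, and presents it as national incidence. The direction is downward as long as some untreated incident cases fall outside the high-risk group, which the baseline design itself allows for. The illustrative undercount is 11% to 37% before detection through records, and it rests wholly on assumed group shares and incidences.

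The effect on hazard ratios is a conditional risk. If the baseline rule is re-applied, factors that are themselves triggers, such as family history and drinking problems, may show upward bias of about 1.1 to 1.4 for a true value of 1, or about 1.05 to 1.27 if records find 30% to 50% of missed cases. The different contact schedules may add to this.

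**What to change.** 1. Label the planned estimate as screen-detected plus treated incidence.
2. Report a corrected estimate beside it. Take stratum-specific miss rates from the baseline 40% and 10% interview samples and carry them into each follow-up year, without counting twice the screen-negative cases already found through records. State the assumption that miss rates for prevalent cases apply to incident cases, and vary it over a range. This also requires the follow-up definition of high risk to be written down, so that the groups are comparable with baseline.
3. For factors that are themselves screening triggers, add a sensitivity analysis restricted to cases found by a symptom-based annual trigger. Keep all SCID-confirmed cases in the primary outcome; removing them would lower an incidence that is already too low.
4. Optionally, within the existing interview total, reserve some follow-up interviews for a small random sample of moderate- and low-risk participants, with inverse-probability weights. This would measure the miss rate for incident cases directly. Repeating the full baseline fractions would need about 11,050 to 13,600 interviews a year under the assumed shares (for example 85,000 × (0.15 × 0.40 + 0.70 × 0.10) = 11,050), so a smaller sample is the realistic form.

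Items 1 to 3 cost a little more analysis work and wider intervals for the corrected incidence. Item 4 changes who is interviewed, so it is a design decision for the investigators.

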#### Sampling method

We will use a multistage stratified random sampling method to identify 17 urban and 17 rural primary sampling sites in 17 of the 31 province-level administrative regions (hereafter, ‘provinces’) in mainland China. The 31 mainland provinces were first stratified by China’s seven administrative regions (Northeast, North, Northwest, East, Central, South and Southwest China) and then specific provinces from all seven geographic regions were selected to be nationally representative of the economic level and population size of the 31 different provinces. The 17 selected provinces included Heilongjiang and Liaoning from Northeast China; Beijing, Hebei, Tianjin, and Shanxi from North China; Gansu, Shanxi and Xinjiang from Northwest China; Zhejiang and Shanghai from East China; Henan, Hunan and Hubei from Central China; Guangdong from South China; and Sichuan and Chongqing from Southwest China.

Within each selected province, the second stage of sampling relied on China’s Disease Surveillance Points (DSP) System, a national representative sampling frame developed by the National Health Commission of the People’s Republic of China starting in 1978 that uses a stratified cluster random sampling method to select surveillance points (i.e., geographic areas that typically includes multiple communities or neighborhoods) around the country [30]. By 2021, a total of 605 points from all 31 provinces were included in this system, with a combined population of over 300 million individuals [30]. The disease surveillance points system provides a nationally representative cohort that has been widely used in national studies about the mortality and morbidity of various diseases [31, 32]. The number of DSP in the 17 selected provinces ranged from 7 (in Tianjin, Beijing and Shanghai) to 27 (in Heilongjiang). The DSP in each province were first stratified as urban or rural (based criteria specified by the National Bureau of Statistics) and then one urban and one rural DSP was selected for each province, resulting in a total 34 DSP. The criteria for selecting DSP within a province included 1) having a mean age of community members similar to that of all urban residents or all rural residents in the province; 2) having qualified mental health providers who were willing to participate in the management of the project; and 3) availability of MRI equipment needed to conduct the imaging part of the assessment.

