#### Sample size

Based on a previous cross-sectional epidemiological study, the prevalence of major depressive disorder among adults in China was 2.1% [33]. Using version 15.0 of the Power Analysis & Sample Size (PASS) package, a sample size of 79,986 is required to identify a condition with a prevalence of 2.1% with a 95% confidence interval of 2.0% to 2.2%. We conservatively decided on a total target cohort of 85,000. This sample will be equally divided between the 34 sampled communities, that is, 2500 individuals in each community. Considering a potential non-response rate of 30% [34], the baseline recruitment will approach at least 3250 adults in each community. Individuals who are lost to follow-up after enrollment will be replaced annually by other individuals who live in the same community, maintaining the cohort size to a minimum of 2500 individuals at each primary sampling site throughout the 5 years of the project.

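### Non-fatal suicidal behaviour and self-harm are scheduled for direct enquiry every 3 months only in diagnosed participants, so ascertainment of this secondary outcome depends on diagnosis

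*Protocol article*

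**What the plan says.** Suicidal and self-harm behaviour are secondary outcomes: "Secondary outcomes include fatal and non-fatal suicidal behavior, other self-harm behaviors, relapses of depression after recovery from a previous episode" (Outcome measurements). That section describes a measurement procedure for depression and ties other mental disorders to the SCID interview. It gives none for suicidal behaviour or self-harm.

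The Follow-up section divides the cohort by diagnosis.

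- **Item C, diagnosed.** Membership is set out as "For participants diagnosed with current or past depressive disorder or other psychiatric disorder based on SCID-5-CV interviews by a psychiatrist at baseline" or during follow-up. For this group: "Every 3 months, telephone calls will be performed by trained researchers to check their depressive symptoms, thoughts of suicide or self-harm, suicide attempts", with other self-harm also covered.
- **Item B, no current or past disorder.** Contact is annual. Diagnoses and treatment in the prior year come from "review of records of the national medical insurance system (which covers all permanent residents); self-reported information about medical treatment for mental disorders", and from the annual GHQ-12 screen and SCID interviews. Online questionnaires follow, with telephone calls to non-responders and to those who report high risk. Suicidal behaviour and self-harm are not mentioned.

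The expanded GHQ-12, described under Enrollment and baseline evaluation, has 12 added items. Two concern suicidal behaviour and the intention of self-harm or suicide. Neither states a period, although several of the other added items do. The Follow-up section calls the annual screen simply GHQ-12 and does not say whether the added items are repeated. Table 1 lists no variable named for suicidal or self-harm behaviour.

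On losses, the Sample size section says: "Individuals who are lost to follow-up after enrollment will be replaced annually by other individuals who live in the same community".

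**The concern.** When one group is asked about an outcome four times a year and the other perhaps once or not at all, recorded rates reflect the asking as well as the behaviour. Here the dividing line is psychiatric diagnosis, the characteristic whose link with suicidal behaviour readers of this cohort will most want to examine.

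Two results are exposed. The cohort-wide rate of non-fatal suicidal behaviour rests mostly on undiagnosed person-time, where detection is weakest. A contrast by diagnosis would mix a real difference with a difference in detection. The intensity of enquiry also changes within a person: an incident case moves from the annual to the quarterly schedule on diagnosis, so a before-and-after comparison has the same problem. Undated events in undiagnosed people cannot be reliably reconstructed afterwards.

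**Working it through.** The article gives no expected rate or precision for suicidal behaviour, so there is no figure of its own to reproduce. The check sets the two schedules side by side and then illustrates the consequence.

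**1. Scheduled direct enquiries over the five-year follow-up**

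| Stream | Per year | Over 5 years |
|---|---|---|
| Diagnosed at baseline (item C) | 4 | 4 × 5 = 20 |
| Diagnosed at the end of year k | 4 after diagnosis | 4 × (5 − k): 16, 12, 8, 4 for k = 1 to 4, plus any annual items before |
| Undiagnosed (item B), added GHQ items repeated | 1 | 1 × 5 = 5 |
| Undiagnosed (item B), added items not repeated | 0 | 0 |

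In person-time this is 4 enquiries per year against 0 to 1. That measures opportunity, not detection.

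**2. What an undated annual item can establish, if it is repeated**

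- Negative before, positive now: a first event can be placed in that interval.
- Already positive at baseline: a later event cannot be recognised.
- Positive at an earlier follow-up: a repeat event cannot be recognised.

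So the favourable reading of item B gives first onsets only, while the quarterly calls each refer to the prior 3 months and can record repeats.

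**3. Effect on a rate ratio (illustration)**

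Let R be the true rate ratio, diagnosed to undiagnosed, and s1 and s0 the shares of events detected in each group. Observed ratio = R × s1/s0. All values of R, s1 and s0 are assumptions; s1 = 0.9 throughout.

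| s0 | s1/s0 | R = 1 | R = 2 |
|---|---|---|---|
| 0.9 | 1.00 | 1.00 | 2.00 |
| 0.7 | 1.29 | 1.29 | 2.57 |
| 0.5 | 1.80 | 1.80 | 3.60 |
| 0.3 | 3.00 | 3.00 | 6.00 |

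**4. Effect on the cohort-wide count (illustration)**

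Let q be the diagnosed share of the cohort. The diagnosed group's share of true events is w = qR/(qR + 1 − q), and the share of all events captured is w × s1 + (1 − w) × s0. With assumed q = 0.10 and R = 5, w = 0.5/(0.5 + 0.9) = 0.357. With s1 = 0.9, capture is 0.771, 0.643 or 0.514 for s0 = 0.7, 0.5 or 0.3. In the middle case the diagnosed group would supply 0.357 × 0.9/0.643 = 50% of recorded events against 36% of true ones.

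**5. Deaths**

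Routes that might reveal a death are insurance records (item B), hospital and public health system records (item C), calls to non-responders (item B), and the description of drop-out reasons (Sampling method). None is designated as the source for suicide deaths, and collection of cause of death is not stated. The replacement rule does not separate deaths from other losses.

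**The case against.** **Closer follow-up of diagnosed people is deliberate.** The design aims to monitor identified episodes closely, and quarterly calls serve that. This stands, and it justifies collecting the quarterly data. It does not make them comparable with annual data.

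**The annual screen is probably the expanded one.** The baseline section uses the short name for the whole two-part screen, and follow-up reuses the high-risk label, which depends on the added items. This is the more natural reading and moves item B from 0 to 5 enquiries. It leaves the missing time window, and the article does not confirm it.

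**Undiagnosed participants have other routes.** Insurance review could show self-harm that reached care. This stands for treated events only.

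**No analysis by diagnosis is specified.** Data analyses names Cox models for the diagnosis of depression and regressions for severity, not a model of suicidal behaviour. This stands: the inflated contrast is conditional on someone making it. The undercount in cohort-wide rates does not depend on that.

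**Stronger readings a reader might infer.**

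- That no source can record a suicide. The routes listed in the working could reveal a death, and naming a cause-of-death source is detail that a condensed article commonly leaves to the full protocol.
- That fatal events are also biased toward diagnosed participants. Nothing shows this; an undesignated source affects both streams.
- That every non-responder is counted as lost and replaced. The article has non-responders telephoned and does not equate the two.

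**Conclusion.** The point holds for non-fatal suicidal behaviour and self-harm. The Follow-up section itself fixes an enquiry schedule that depends on diagnosis: 4 direct enquiries per person-year in the diagnosed stream against none, or at most 1 undated one, in the undiagnosed stream. The likely direction is under-detection in undiagnosed participants, hence cohort-wide rates that are too low and ratios by diagnosis that are too high. The direction rests on the assumption that less frequent or absent asking detects fewer events. The size cannot be computed from the article; the ratios of 1.29 to 3.00 for a true ratio of 1 come only from the assumed detection shares, and equal detection would give no distortion of the ratio. To say that the association is inflated by design would go too far, since neither the detection difference nor the comparison is stated.

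For deaths, the supported statement is narrow: the article designates no source for suicide or cause of death and does not separate deaths from replaced losses.

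**What to change.** 1. Add one identical, dated question on suicidal behaviour and self-harm, referring to the time since the last annual assessment, to the annual questionnaire of both streams. It should record whether an event occurred, the approximate date and the number of events.
2. State in the analysis plan that cohort-wide rates and any comparison between diagnosed and undiagnosed participants use only that annual answer, and that the quarterly answers describe course within diagnosed participants.
3. State whether the 12 added GHQ items are repeated each year.
4. If the full protocol does not already do so, name the source for suicide deaths and classify deaths separately from the losses that are replaced. The surveillance points used for sampling are described as "widely used in national studies about the mortality and morbidity of various diseases", so their death data are a natural candidate. Access must be confirmed.

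Items 1 to 3 cost one or two questions in an existing questionnaire and some between-group use of the quarterly data. The common question reduces the bias but may not remove it, because people telephoned every quarter may recall or report more readily. Item 4 costs more if it means linkage: Data storage keeps identifying details on paper at the 17 centers, and the consent options listed under Ethics and dissemination do not mention death records. The Quality control section allows procedures to be revised after the site pilots, which is the natural time for these changes.
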